**11.3 Sample size considerations**

The target sample size for the number of participants at each study site is calculated to test the hypothesis Ho: [PPV ≤ (disease prevalence + α) or NPV ≤ (1-disease prevalence)] with 80% power and 5% significance at each study location. For the higher transmission sites of Uganda and Burkina Faso α=0.4, while α=0.3 for Nigeria. Previously published estimates of sensitivity (65%) and specificity (98%) were used in these calculations.

Using the target sample sizes outlined below the study will be powered to detect changes in infant birth weight and maternal Hb of >85g and 0.34g/dl, respectively. The sample size for the Burkina Faso site should also allow detection of changes in infant birth weight (>123g) with sufficient power. Based on published data, other sites will not be individually powered to detect likely changes in birth weight (~123g) and none of the sites will be individually powered to detected likely changes in maternal Hb (~0.4g/dl). However this will not prohibit any of the statistical analysis planned.

We estimate that the statistical requirements of the study can be met by enrolling 345 women at the high-transmission Ugandan site, 460 women at the low-transmission Nigerian site, and 860 women at the seasonal-transmission site in Burkina Faso, for a total sample size of 1,665 participants. This estimate assumes a 15% loss to follow-up at each study location.

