**2 STUDY OVERVIEW AND PROTOCOL SUMMARY**

Study population: Women presenting for routine antenatal care in the second and third trimesters of pregnancy.

Number of Sites: Antenatal clinics at ≥3 sites of varied malaria transmission intensity in Africa; proposed collaborating sites in Burkina Faso, Nigeria, and Uganda. (NB: At present, funds are available to complete the study in two sites, in Burkina Faso and in Uganda; if additional resources permit in the future, the study will also be implemented at the Nigerian site.)

Study Duration: Approximately 12 months from the start of study activities at each site, depending on rates of enrollment.

General objective: To determine whether screening pregnant women for malaria with RDTs may detect placental infection and predict risk of poor birth outcomes due to malaria in areas of varied malaria transmission in Africa.

Specific primary objectives:

1. To compare the results of RDTs, microscopy and PCR performed on peripheral blood from women in the second and third trimesters of pregnancy in malaria-endemic areas of Africa.
2. To determine the positive and negative predictive values of results of RDTs, microscopy and PCR performed on peripheral blood from women in the second and third trimesters of pregnancy, as compared with evidence of placental infection by histological examination after delivery.

Specific secondary objectives:

1. To measure and compare the frequency of pregnancy outcomes (infant birth weights, maternal hemoglobin), prevalence of placental malaria, and risk of symptomatic malaria among women in the study cohort. Participants who test positive by RDT at the time of usual IPTp administration will receive artemisinin-combination treatment (ACT) or quinine; participants who test negative by RDT will receive standard-of-care IPTp with SP.
2. To collect samples for future laboratory analyses related to malaria in pregnancy, including the measurement of the prevalence of molecular markers of antimalarial resistance in the study cohorts.

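### The pooled power for birth weight and Hb in section 11.3 is stated for 1,665 women at three sites; section 2 says only two sites, totalling 1,205, are funded at present, and no two-site figure is given

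*Protocol*

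**What the plan says.** Protocol section 11.3 introduces its power statement for the two continuous outcomes with "Using the target sample sizes outlined below" and concludes that "the study will be powered to detect changes in infant birth weight and maternal Hb of >85g and 0.34g/dl". The targets in question are "345 women at the high-transmission Ugandan site, 460 women at the low-transmission Nigerian site, and 860 women at the seasonal-transmission site in Burkina Faso"; the section puts their sum at 1,665. On attrition it says "This estimate assumes a 15% loss to follow-up at each study location".

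Protocol section 2 limits what can be carried out now: "At present, funds are available to complete the study in two sites, in Burkina Faso and in Uganda". The third site is contingent: "if additional resources permit in the future, the study will also be implemented at the Nigerian site".

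Other sections bear on this:

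- Section 11.1 lists mean birth weight and mean maternal Hb among three primary outcomes.
- Section 11.2 compares RDT-positive women given ACT or quinine with RDT-negative women given SP.
- Section 11.4 has each site recruit to its own target, so nothing moves Nigeria's 460 women elsewhere.

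**The concern.** Section 11.3 states the pooled power as a property of the study and does not mention that 460 of the 1,665 women depend on money not yet in hand. A reader of that section alone would credit the funded study with a precision it does not have.

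This affects two of the three primary outcomes. Pooling matters most for Hb, because section 11.3 concedes that no single site is powered for the change it regards as likely (about 0.4 g/dL). The pooled sample is therefore the only source of adequate power for Hb, and it is the pooled sample that shrinks without Nigeria.

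**Working it through.** **Inputs from the protocol.** Site targets are 345 (Uganda), 460 (Nigeria) and 860 (Burkina Faso), with 15% loss at each (section 11.3). The pooled detectable differences are 85 g and 0.34 g/dL; the likely changes are about 123 g and about 0.4 g/dL (section 11.3). The funded sites are Burkina Faso and Uganda (section 2).

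**Assumptions.** The 80% power and 5% significance are stated for the predictive-value test ("with 80% power and 5% significance at each study location"); I assume they also apply to birth weight and Hb. I assume a common SD across sites. Sidedness is not stated, so both versions are shown where it matters.

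**Step 1: sample sizes.**
- Three sites: 345 + 460 + 860 = 1,665; × 0.85 = 1,415 evaluable.
- Two sites: 345 + 860 = 1,205; × 0.85 = 1,024 evaluable.
- Reduction: 460/1,665 = 28%.

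**Step 2: can the 85 g be reproduced?** Not directly, because the SD and RDT-positive share are not given. An indirect check uses the fact that, at a fixed SD and group split, the detectable difference scales as 1/√N. Section 11.3 also gives 123 g for Burkina Faso alone (860 women).
- If 85 g belongs to 1,665: 85 × √(1,665/860) = 118 g for Burkina Faso.
- If 85 g belongs to 1,205: 85 × √(1,205/860) = 101 g for Burkina Faso.

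The first is close to 123 g and the second is not. This agrees with the text, which ties 85 g to the listed targets. It is supporting evidence only, since 123 g is also the plan's likely change and need not be a computed limit.

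**Step 3: two sites, equal RDT positivity.** The standard error grows by r = √(1,665/1,205) = 1.1755.
- Birth weight: 85 × 1.1755 = 99.9 g.
- Hb: 0.34 × 1.1755 = 0.400 g/dL.
- Power for 85 g or 0.34 g/dL, two-sided: Φ(2.802/1.1755 − 1.960) = Φ(0.424) = 66%.
- One-sided: Φ(2.486/1.1755 − 1.645) = Φ(0.470) = 68%.

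**Step 4: two sites, low positivity in Nigeria.** The comparison is RDT-positive against RDT-negative, so a site with few positives adds less information. Assumed shares are Uganda 15-40%, Burkina Faso 15-30% and Nigeria 3-10%. The 15% loss is the same at every site and cancels from r.
- *Smallest loss* (40%, 30%, 3%; site-stratified, information Σ n·p·(1−p)): Uganda 82.8, Burkina Faso 180.6, Nigeria 13.4. r = √(276.8/263.4) = 1.025, giving 87 g, 0.35 g/dL and 78% power.
- *Largest loss* (15%, 15%, 10%; pooled): two sites have 180.75 positives and 1,024.25 negatives; three sites have 226.75 and 1,438.25. r = √(1/180.75 + 1/1,024.25) ÷ √(1/226.75 + 1/1,438.25) = 0.08068/0.07145 = 1.129, giving 96 g, 0.38 g/dL and 70% power.

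Both powers are two-sided.

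**Step 5: power for the changes the plan calls likely (equal shares, two-sided).**
- 123 g: Φ(2.802/1.1755 × 123/85 − 1.960) = 93%, against 98% with three sites.
- 0.4 g/dL: Φ(2.802/1.1755 × 0.4/0.34 − 1.960) = 80%, against 91% with three sites.

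| Case | Birth weight at 80% power | Hb at 80% power | Power for 85 g / 0.34 g/dL |
|---|---|---|---|
| Three sites, as stated | 85 g | 0.34 g/dL | 80% (assumed) |
| Two sites, low Nigerian positivity | 87-96 g | 0.35-0.38 g/dL | 70-78% |
| Two sites, equal positivity | 100 g | 0.40 g/dL | 66-68% |

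**The case against.** The best defence is that nothing printed is numerically wrong. The three targets do sum to 1,665, the power sentence is tied to those targets, and section 2 discloses the funding position openly. On this view the plan is a three-site design with a caveat that section 11.3 does not repeat. That stands: a reader might infer an arithmetic error, and there is none. What remains is two sections that have not been reconciled.

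A reader might also infer that the study that runs will lack the stated power. The protocol does not settle this. Its funding note describes the present position and leaves Nigeria open, so the claim can be made only about the currently funded design.

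It is tempting to lead with 100 g and 66%. Those figures assume equal positivity, whereas section 7.1.1 describes the Nigerian site as low-transmission. They are close to a worst case and serve as an upper bound on the loss.

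The practical effect is also limited. Section 11.3 sizes each site separately for the predictive-value hypothesis, so the Ugandan and Burkinabe calculations are untouched. Even with equal shares, power for the likely changes stays at conventional levels.

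Finally, a reader might infer that the aim of covering varied transmission collapses. It does not: section 7.1.1 gives Burkina Faso seasonal and Uganda high year-round transmission. The low end would be lost, but section 2 makes that contingency visible.

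None of this supplies the missing two-site figure.

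**Conclusion.** The concern holds as a mismatch between sections 2 and 11.3. The stated 85 g and 0.34 g/dL describe the 1,665-woman design, and the currently funded design has 1,205. Under a common SD, the stated figures are too favourable for the funded sample in every case examined, by about 3% to 18%.

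The exact size cannot be fixed from the protocol. The range rests on the assumed positivity shares, on 80% power and 5% significance applying to these outcomes, and on unstated sidedness.

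The consequence is moderate. In the equal-share case birth weight keeps ample power for the likely change, but Hb is left at about 80% for 0.4 g/dL with no reserve. The documents do not support saying that the study is inadequately powered for the changes it considers likely. They support saying that a stated property of two primary outcomes is not delivered by the sample currently funded.

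**What to change.** In section 11.3, recompute and state the pooled detectable differences for the funded two-site sample (1,205 enrolled, about 1,024 evaluable). Use the sponsor's own SDs and site-specific RDT-positive shares, and print those inputs with the power, significance level and sidedness. On the assumptions above, the result should fall at about 87-100 g and 0.35-0.40 g/dL at 80% power, but the sponsor's inputs should determine the printed values. Keep 85 g and 0.34 g/dL, labelled as conditional on the Nigerian site being funded, with a cross-reference to section 2.

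The cost is a few lines of text and slightly less favourable stated figures. No extra participants are needed, and the per-site targets do not change.

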**11.4 Participant enrollment and follow-up**

Recruitment and enrollment will include all eligible pregnant women who present for routine antenatal care in their second or third trimester (sections 6, 7.2.1). Recruitment will continue at each site until the target sample size given in Section 9.3 is reached.

**12 QUALITY ASSURANCE**

Quality control and assurance of all diagnostic tests will be conducted according to SOPs and as briefly described in sections 7.6.2.1, 7.6.3.2, 7.6.4 and 7.6.7. To ensure the quality and integrity of data, and the safety of participants, an independent study monitor will be contracted for the duration of the study as in section 8.3.

**13 EXPECTED OUTCOMES OF THE STUDY**

Malaria prevention measures for use during pregnancy, including insecticide-treated nets and IPTp are available and effective. However, increasing parasite resistance to SP- IPTp raises concerns that this approach will soon lose effectiveness. Screening with rapid diagnostic tests (RDTs) may offer an accurate and practical way to identify pregnant women who will benefit from targeted therapy for placental malaria infection. This study proposes to assess the efficacy of well-characterized RDTs in detection of placental malaria, to provide data necessary for future evaluations of screening and targeted treatment as a potential alternative to the failing regimen of IPTp with SP. If RDTs are shown to be accurate in detecting placental malaria, it will provide new evidence to support interventions such as IST (intermittent screening and treatment) in further research and in malaria control policy.

**14 DISSEMINATION OF RESULTS AND PUBLICATION POLICY**

Data collected in this study will be compiled, analyzed and made available to collaborating partners, ministries of health in participating countries, the WHO, and will be prepared for publication in a peer-reviewed journal. Study staff and health center staff will be informed of overall study results after data analysis has been completed. Summarized study results may be posted in the participating health centers for review by participants. Results of the study may be publicized in the future by collaborating partners and stakeholders as part of public health education efforts and malaria control programs.

**15 DURATION OF THE PROJECT**

The duration of participant recruitment and follow-up is expected to take approximately 12 months from the start of study activities at each site, depending on rates of enrollment.

**Table 1. Proposed study timeline**

| Activity | Mo 1-3 | | Mo 4-6 | Mo 7-9 | Mo 10-12 | Mo 13-15 | Mo 16-18 |
| --- | --- | --- | --- | --- | --- | --- | --- |
| Study/site prep, training |  | |  |  |  |  |  |
| Pilot, begin enrollment |  |  |  |  |  |  |  |
| Enroll to sample size |  |  |  |  |  |  |  |
| Participant follow-up |  | |  |  |  |  |  |
| Quality control of diagnostic test results |  | |  |  |  |  |  |
| Completion of PCR |  | |  |  |  |  |  |
| Data cleaning, analysis |  | |  |  |  |  |  |
| Report writing |  | |  |  |  |  |  |

**16 PROBLEMS ANTICIPATED**

**Table 2. Potential study problems and proposed solutions**

| **Potential problem** | **Proposed solution** |
| --- | --- |
| Insufficient sample size, or slower than expected enrollment | 1) Increase number of clinical sites (within the same geographical/population area)  2) Publicize study through locally appropriate communication channels |
| High (>15%) loss to follow-up | 1) Reinforce importance of full follow-up in informed consent discussion and at study visits  2) Increase home visit staff |
| Major discrepancies in validation and quality control of diagnostic test results | 1) Discuss with co-investigators to identify reason/s: poor equipment/lab supplies, personnel error, etc.  2) Address cause with replacement of equipment/supplies, refresher training, personnel replacement if necessary, or other as appropriate |
| Adverse events and/or protocol violations | Report to appropriate ethical committee and DSMB; prevention as appropriate through protocol amendment and/or personnel training |

**17 ETHICAL CONSIDERATIONS AND PARTICIPANT CONFIDENTIALITY**

Ethical approval will be sought from the WHO and from national/institutional review committees in all participating countries. Written informed consent will be obtained from all participants as described in section 7.2. Participants will be identified by coded study numbers rather than names in all data collection forms and electronic databases. No individual identities will be used in any reports or publications resulting from the study. Only study staff and study investigators will have access to the information collected, for purposes of data entry and analysis. At the time of informed consent for study participation, participants will be informed that participation in a research study may involve a loss of privacy; however, for this study no sensitive information will be collected, and only study personnel will have access to the information collected.

REFERENCES

**2.** WHO/AFRO. *A strategic framework for malaria prevention and control during pregnancy in the African region.* Brazzaville: World Health Organization, Regional Office for Africa; 2004. AFR/MAL/O4/01.

**3.** Desai M, ter Kuile FO, Nosten F, et al. Epidemiology and burden of malaria in pregnancy. *Lancet Infect Dis.* Feb 2007;7(2):93-104.

**5.** Rogerson SJ, van den Broek NR, Chaluluka E, Qongwane C, Mhango CG, Molyneux ME. Malaria and anemia in antenatal women in Blantyre, Malawi: a twelve-month survey. *Am J Trop Med Hyg.* Mar 2000;62(3):335-340.

**7.** ter Kuile FO, Parise ME, Verhoeff FH, et al. The burden of co-infection with human immunodeficiency virus type 1 and malaria in pregnant women in sub-saharan Africa. *Am J Trop Med Hyg.* Aug 2004;71(2 Suppl):41-54.

**8.** Brabin BJ. An analysis of malaria in pregnancy in Africa. *Bull World Health Organ.* 1983;61(6):1005-1016.

